### Data collection and management

2.15

eCRF completion: Data must be sourced from original documents. All data must be entered in a timely, accurate, complete, standardized, and truthful manner. No items should be left blank. Any corrections must be documented with the reason for change.eCRF review: The clinical research coordinator (CRC) will promptly complete, review, and submit the eCRF, and respond to queries raised by the data manager or clinical research associate (CRA). After data cleaning, the principal investigator will sign to confirm the data.EDC database: A study-specific EDC database will be designed. User acceptance testing (UAT) will be completed before the enrollment of the first patient. All users must complete training before accessing the database.Data entry and verification: Data will be promptly entered and submitted after each visit. The data manager and medical reviewer will review the data and issue queries. After the investigator responds to the queries, the data will be confirmed.Medical coding: Adverse events will be coded using the latest Chinese version of the Medical Dictionary for Regulatory Activities (MedDRA). Concomitant medications will be coded using the second edition of the *Dictionary of Contemporary Drug Trade Names and Aliases*.Blind review and unblinding: After all data tasks are completed, a blind review meeting will be convened to determine the analysis populations and lock the database. After the database is locked, the first unblinding will be performed, during which the statistician will be unblinded only to Group A versus Group B (without knowing which group is SXYX or placebo), followed by statistical analysis. At the final study meeting, the second unblinding will be performed with all participants (investigators, sponsor representatives, and the statistician) together, after which the study report will be signed and finalized.Wearable Device Data Collection and Management1) Device information: Maiya Smart ECG Ring (Maiya Technology, China, model TK30). The device is equipped with a high-performance ECG sensor (GH3228), a PPG sensor (GPSE1602B), and an accelerometer (SC-7A20H), and is compatible with Android 9.0 and iOS 10.0 and above. 2) Pre-trial validation study: To ensure the reliability of data obtained from the wearable device in the target HFpEF population, a pre-trial validation study will be conducted before the main trial is initiated. A total of 32 patients who meet the trial entry criteria (8 from each sub-centre) will be enrolled. Each participant will undergo standard 12-lead electrocardiography (ECG) and pulse oximetry monitoring while wearing the device. Data will be collected under two conditions: (i) at rest (10 min in the supine position), and (ii) immediately after the 6-minute walk test (6MWT). The validation will assess: (i) heart rate accuracy: Bland–Altman analysis will be performed to calculate the mean bias and limits of agreement between the device-derived heart rate and that from the 12-lead ECG; the device will be considered acceptable if the mean absolute error for heart rate is ≤5 beats/min; (ii) oxygen saturation accuracy: the device-recorded SpO_2_ will be compared with that from pulse oximetry, with an acceptable mean absolute error of ≤2%; (iii) step count (distance): device-recorded data will be compared with the actual distance walked during the 6MWT, with an acceptable mean absolute error of ≤5%. 3) Wear time: Participants will wear the ring continuously for 1 week at baseline, week 12, and week 24. To ensure adequate data acquisition, at least 4 valid days are required at each assessment time point. A valid day is defined as a day with wear time ≥23 h (objectively verified by the device's accelerometer and skin-contact sensor) and ≥8 h of valid signal recording. 4) Data quality standards: Within each valid day, at least 8 h of valid ECG/PPG recordings (excluding artefact-contaminated segments) are required. If more than 30% of the recorded signal is classified as artefact (e.g., motion artefact, poor skin contact, or electrical interference), the data from that day will be excluded from analysis. All device-derived data will be reviewed by a blinded central core laboratory, and a random 10% sample will be subjected to additional manual quality checks to ensure inter-rater reliability. 5) Handling of missing data: Multiple imputation (MI) will be employed under the assumption of conditional missing at random (MAR), given the covariates included in the analysis model (baseline values, treatment allocation, visit time) and previous observed values. The imputation model will include all covariates used in the descriptive analysis model for the wearable device data, and will incorporate auxiliary variables that influence the missingness mechanism (e.g., signal quality flags, wear logs) to improve precision. Imputation will be performed only for measures that are complete at baseline but missing at subsequent visits (week 12 or week 24) due to <4 valid days; subjects with complete baseline data missing will not be included in the primary MI analysis, but will be retained in the modified intention-to-treat (mITT) set for other endpoint analyses. Twenty imputed datasets will be generated; the descriptive analysis model will be fitted to each, and the estimates and standard errors will be pooled using Rubin's rules. To explore the potential impact of the MAR assumption on the trend of results within an exploratory framework, a worst-case exploratory scenario analysis will be conducted: missing values in the intervention group will be replaced by the group observed mean +2 standard deviations (in the direction of worsening), and those in the control group by the group observed mean −2 standard deviations (in the direction of improvement). The results of this scenario analysis will be reported descriptively, comparing whether the direction and magnitude of the effect estimates are consistent with those of the primary analysis; all results will be clearly labelled as exploratory, with no formal statistical significance testing or adjustment for multiplicity. 6) Derived outcome measures: Mean heart rate, step count (distance), oxygen saturation, heart rate variability, and nocturnal sleep duration.

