The major innovation of this study lies in the following aspect: Given that traditional cardiopulmonary exercise testing can only be performed in a hospital setting and cannot reflect patients’ daily exercise tolerance, this study overcomes the limitations of the traditional single-modality assessment of exercise tolerance in HFpEF patients by introducing wearable monitoring devices to achieve out-of-hospital, real-time, long-term, and dynamic capture of patients’ cardiopulmonary exercise data, including heart rate, blood oxygen saturation (SpO_2_), step count, walking distance, and other parameters, thereby establishing a comprehensive evaluation model consisting of in-hospital standardized assessment plus out-of-hospital long-term dynamic monitoring. This model will evaluate the clinical efficacy of SXYX in treating HFpEF from multiple dimensions. Meanwhile, the protocol has been designed in strict accordance with the SPIRIT 2025 guidelines to ensure the generation of high quality clinical evidence. In summary, this study will provide an objective, pragmatic, and patient centred evaluation of the therapeutic efficacy of SXYX in a real world setting, thereby offering high level evidence to support their clinical application. Future research should focus on exploring the integration of wearable-derived digital biomarkers into routine clinical decision-making for HFpEF.

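### The wearable day-exclusion rule ties step count to ECG/PPG signal quality, so it may selectively drop active days and attenuate a step-count gain (minor)

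*Protocol article*

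**What the plan says.** All of the following stands in the wearable-device paragraph of section 2.15 (Data collection and management) of the protocol article.

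- Item 1 lists three sensors: ECG, PPG and an accelerometer.
- Item 3: "A valid day is defined as a day with wear time ≥23 h", together with 8 h of valid signal. Over each one-week wearing period, "at least 4 valid days are required at each assessment time point".
- Item 4 frames quality in terms of the cardiac and optical channels: "at least 8 h of valid ECG/PPG recordings (excluding artefact-contaminated segments) are required". It continues: "If more than 30% of the recorded signal is classified as artefact (e.g., motion artefact, poor skin contact, or electrical interference"), then "the data from that day will be excluded from analysis". No measure is exempted.
- Item 5 imputes a week-12 or week-24 value only where fewer than 4 valid days remain. It assumes missing at random and uses signal-quality flags and wear logs as auxiliary variables. An exploratory scenario analysis shifts missing values by 2 SD, towards worsening in the intervention group and towards improvement in the control group.
- Item 6 lists the derived measures: "Mean heart rate, step count (distance), oxygen saturation, heart rate variability, and nocturnal sleep duration".

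Section 3 (Discussion) presents the wearable data as the study's main innovation, on the ground that hospital exercise testing "cannot reflect patients’ daily exercise tolerance, this study overcomes the limitations of the traditional single-modality assessment".

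**The concern.** Movement is both what step count measures and the first named cause of the artefact that voids a day. Motion degrades an ECG or PPG trace, whereas for an accelerometer it is the signal. One day-level rule for all measures therefore lets poor cardiac or optical signal delete a day's steps.

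If artefact rises with activity, a day is more likely to be lost when its step count is high, which is selection on the outcome. An effective treatment would raise activity in one arm, so that arm would lose more days and more patients, and the observed gain would be pulled towards zero. At stake is the interpretation of the out-of-hospital activity result. The peak VO2 analysis is not affected.

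**Working it through.** **No figure to reproduce.** The document gives no effect size, SD, artefact rate or activity-artefact relation for the wearable outcomes. The size can only be explored under assumptions.

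**Threshold arithmetic.** Suppose signal is recorded throughout a 23 h day.
- Artefact needed to reach the cut-off: 0.30 × 23 = 6.9 h.
- Clean signal on a retained day: at least 0.70 × 23 = 16.1 h.
- A day with only 8 h clean would have 1 − 8/23 = 65% artefact.

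On this assumption the 30% rule decides and the 8 h minimum does not. The 8 h minimum becomes the deciding limit once recorded signal falls below 8/0.70 = 11.4 h.

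**Do the planned safeguards cover the problem?**
- 4 to 6 days kept: the visit value is the mean of the kept days. Item 5 does not impute it, so nothing corrects it if the dropped days were the active ones.
- Fewer than 4 days kept: imputation applies. The signal-quality flags may help, but the model learns from step values that the same rule has already filtered.
- Scenario analysis: missing SXYX values move only towards worsening, so the case in which they are high is never examined.
- Device validation (item 2): agreement is checked at rest and immediately after the 6-minute walk. The artefact share of an active day is not measured.

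**Simulation A.** Assumed: mean 5000 steps/day, between- and within-patient SD 1500 each, true gain 750, 7 days per week. Artefact share is 10% plus a slope per 1000 steps, with noise SD 5 points. A day is dropped above 30%, and a patient is kept with at least 4 days. There is no imputation.

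| Slope (points per 1000 steps) | Observed/true, follow-up means | Observed/true, change from baseline |
|---|---|---|
| 2 | 0.91 | 0.94 |
| 3 | 0.56 to 0.57 | 0.81 to 0.82 |
| 4 | 0.34 to 0.35 | 0.70 to 0.71 |

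Ranges are simulation error between runs. At slope 3, 73% of control days and 63% of SXYX days are valid, and 82% and 69% of patients keep at least 4 days. The change-from-baseline column is the fairer one, because the plan's imputation and analysis models condition on baseline values.

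**How steep can the slope be?** On 23 h of recording, 3 points is 0.03 × 23 × 60 = 41 minutes of lost signal per 1000 steps. At an assumed 60 to 100 steps per minute, 1000 steps take 10 to 17 minutes. If every walking minute were artefact, the slope would be 10/1380 to 16.7/1380, or 0.7 to 1.2 points. With slopes in that range and the other inputs unchanged:
- Follow-up means: about 0.87 to 1.00 of the true gain.
- Change from baseline: about 0.95 to 1.00. The low end arises only when mean artefact is already 25% at 5000 steps.

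**Simulation B (different inputs, change from baseline).** Assumed: between-patient SD 2000, day-to-day SD 1500, gain 500 or 1000, noise SD 7 points, slope 3 to 5 points per 1500 steps (2 to 3.3 per 1000).

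| Mean artefact | Observed/true |
|---|---|
| 10% | 0.95 to 0.99 |
| 20% | 0.88 to 0.95 |
| 25% | 0.85 to 0.92 |

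At 25%, up to 44% of SXYX days are dropped and up to 42% of SXYX patients fall below 4 valid days at follow-up. With no link between artefact and activity the ratio is 1.00, even with 24% of days dropped.

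**The case against.** The strongest reply is that the bias needs a link that the document does not establish. Motion is one of three example causes, and poor skin contact and electrical interference need not follow activity. On continuous recording it takes about 6.9 h of artefact to void a day. The source of the step count is not stated. All of this stands, and it is why the point is put conditionally.

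Second, imputation uses signal-quality flags, which bear directly on why days are lost. This stands in part: the flags may help below 4 valid days, but patients with 4 to 6 days are not imputed at all.

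Third, the wearable measures are absent from the primary and secondary outcome lists (sections 2.14.1 and 2.14.2) and from the fixed testing sequence (section 2.18). Section 2.15 calls their analysis model descriptive. This stands and sets the severity.

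A reader might also infer more than the text supports:
- That the most active days are bound to be deleted, or that half or more of a gain would vanish. The ratios near 0.56 and 0.35 compare follow-up means only. They need slopes of 3 or 4 points, which put an average 5000-step day at 10 + 15 = 25% or 10 + 20 = 30% artefact, close to or at the cut-off.
- That the 30% and 8 h limits contradict each other. They do not: the 8 h limit is idle only if signal is recorded throughout wear, and no recording duration is stated.
- That the 23 h wear rule is itself an error. Nocturnal sleep duration is a derived measure and needs overnight wear, and nothing in the document shows that charging or washing takes more than 1 h.

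**Conclusion.** The point holds as a minor, conditional one. As written, the rule lets ECG/PPG artefact delete a day's step count. If artefact rises with activity, it may selectively remove active days, more often in the more active arm, and attenuate a gain in steps. The planned imputation does not correct patients with 4 to 6 kept days, and the scenario analysis does not probe high missing values in the SXYX group.

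The size is unknown. Under the assumed inputs the loss in change from baseline is between nil and about 30%, and about 0 to 5% at roughly 1 point of artefact per 1000 steps. These figures rest on assumed step means and SDs, artefact level and slope, on the accelerometer being the source of steps, and on no imputation. No confirmatory conclusion of the trial depends on the point.

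**What to change.** In section 2.15, make validity specific to each measure:

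1. Apply the 30% artefact rule and the 8 h signal rule only to the measures taken from ECG/PPG: heart rate, SpO2 and heart rate variability.
2. State which sensor yields step count and distance. If it is the accelerometer, judge their valid days by accelerometer-verified wear time alone.
3. Keep the minimum of 4 valid days, counted separately for each measure.
4. Report the number of excluded days by arm and visit, so that any imbalance is visible.

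If days with poor ECG/PPG signal were always meant to keep their step counts, one sentence saying so removes the concern.

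The cost is a few lines of text and separate validity flags in the device data. The downside is that the number of valid days, and so the number of patients analysed, will differ between measures. Making the change before data accrue avoids a post-hoc choice of rule.

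### Wearable imputation rule (section 2.15, item 5) can discard valid week-12 and week-24 recordings only because the baseline week does not qualify, although that baseline could be imputed in the same model

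*Protocol article*

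**What the plan says.** All the relevant text is in section 2.15 of the protocol article, under wearable device data.

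- **Wear periods (item 3):** "Participants will wear the ring continuously for 1 week at baseline, week 12, and week 24". On completeness, "at least 4 valid days are required at each assessment time point". On validity, "A valid day is defined as a day with wear time ≥23 h", with at least 8 h of valid signal also required.
- **Data quality (item 4):** a day with more than 30% artefact is excluded.
- **What is imputed (item 5):** "Imputation will be performed only for measures that are complete at baseline but missing at subsequent visits". A follow-up measure counts as missing when it is "missing at subsequent visits (week 12 or week 24) due to <4 valid days".
- **Who is left out (item 5):** "subjects with complete baseline data missing will not be included in the primary MI analysis". The sentence goes on: "but will be retained in the modified intention-to-treat (mITT) set for other endpoint analyses".
- **Models (item 5):** baseline values, treatment allocation and visit time are named as covariates of the analysis model. Twenty imputed datasets are pooled by Rubin's rules.

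**The concern.** The exclusion turns on a covariate, not on the outcome. A patient may have full, valid ring recordings at weeks 12 and 24, which are the data the comparison is about, and still be left out because the first wear week fell short. Multiple imputation is already planned and can fill a missing baseline from the follow-up values and the other covariates, so the exclusion is not needed.

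Falling short at baseline is plausible under the plan's own definitions. Slightly more than one hour off the finger invalidates a day, and four such days in seven leave only three valid ones.

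The exclusion sentence can also be read in two ways. It may mean that baseline is not complete (0 to 3 valid days) or that it is wholly absent (0 valid days). The choice decides who is analysed.

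At stake are the precision and the clear definition of the wearable comparison, which the Discussion presents as the study's major innovation.

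**Working it through.** **The plan's own figures.** The article gives no expected share of incomplete wearable weeks and no precision target for wearable measures, so there is no wearable figure to reproduce. The only input from the plan is the total of 148. It follows from section 2.2: 2 × (1.96 + 1.282)² × 20.34 / 2.7² = 58.65, rounded up to 59 per group; 59 / 0.8 = 73.75, rounded up to 74 per group; 148 in total. That calculation concerns peak VO2 and does not bear on this point.

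**What each reading does to a patient with valid follow-up weeks.**

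| Valid baseline days | Exclusion read as baseline not complete | Exclusion read as baseline wholly absent |
|---|---|---|
| 4-7 | analysed | analysed |
| 1-3 | excluded | not imputed, not expressly excluded |
| 0 | excluded | excluded |

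The text needs correcting on either reading.

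**Cost in precision.** Assumed inputs:

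- m is the share of patients with valid follow-up who lack a qualifying baseline: 5%, 20% or 30%.
- ρ is the baseline/follow-up correlation: 0.5 or 0.7.

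Standard errors (SE) are relative to complete data:

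- Dropping these patients: 1/√(1 − m).
- Keeping them without their own baseline: 1/√[(1 − m) + m(1 − ρ²)] = 1/√(1 − mρ²). Each such patient contributes information 1 − ρ² instead of 1.
- Avoidable increase, dropping against keeping: √[(1 − mρ²)/(1 − m)].

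| m | Patients left of 148 | Dropped vs complete data | Dropped vs kept, ρ = 0.5 | Dropped vs kept, ρ = 0.7 |
|---|---|---|---|---|
| 5% | 141 | 1.026 | √(0.9875/0.95) = 1.020 | √(0.9755/0.95) = 1.013 |
| 20% | 118 | 1.118 | √(0.95/0.80) = 1.090 | √(0.902/0.80) = 1.062 |
| 30% | 104 | 1.195 | √(0.925/0.70) = 1.150 | √(0.853/0.70) = 1.104 |

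The last two columns give the avoidable loss: about 1-2%, 6-9% and 10-15%. The column against complete data overstates it, because no analysis can recover a baseline that was never recorded. The approximation ignores the small extra noise from using 20 imputations. Patients with neither a baseline nor a follow-up week add nothing under either approach. If those two failures go together, m is smaller than the raw share without a baseline.

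**Follow-up weeks with 1 to 3 valid days.** The reliability of a k-day mean is k·ICC/(1 + (k − 1)·ICC). At an assumed single-day ICC of 0.5 this is 0.50, 0.67, 0.75 and 0.80 for 1, 2, 3 and 4 days. I compared imputing such weeks from baseline and week 12 with using their raw means unweighted. The assumptions were 10-30% of patients affected, ICC 0.3-0.7, and correlation between true person-level values 0.7-0.9. With imputation, the week-24 SE is 1.5-14% larger for 3-day weeks, from 1% smaller to 12% larger for 2-day weeks, and from 14% smaller to 7% larger for 1-day weeks. Neither approach is better throughout.

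**The case against.** The strongest reply is that this is a descriptive analysis with a pre-specified data-quality rule, and that little hangs on it. Much of that stands. Item 5 calls the wearable model descriptive. Wearable measures appear in none of the outcome lists in section 2.14 and not in the testing sequence of section 2.18. The explicit exploratory label stands next to the worst-case scenario and may have been meant for that alone, but nothing in the article gives the wearable results a confirmatory role. No missing rate is documented either, so a material loss is possible but not shown.

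A reader might infer more than the text supports:

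- **That any imperfect baseline week removes a patient.** It does not: 4 to 6 valid days of 7 qualify.
- **That these patients leave the trial analysis.** They do not: the same sentence keeps them in the mITT set for other endpoints.
- **That observed days in a short follow-up week are wrongly overwritten by predictions.** A 4-day minimum is a defensible quality rule, and the list of "auxiliary variables that influence the missingness mechanism (e.g., signal quality flags, wear logs) to improve precision" is open-ended, so it does not show that those days go unused. As calculated above, one or two noisy days used unweighted can be less precise than imputation. Adding the mean of the 1 to 3 available days as a predictor is also not estimable as such, because patients with 4 or more valid days have no such quantity.
- **That patients are removed for behaviour after allocation.** Table 3 marks the wearable at Visit 2, the randomisation visit, and not at Visit 1. The exact days of the baseline week are not stated, so this remains a conjecture and bias is not shown.

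None of this answers the remaining point: outcome data are left out for want of a covariate that the planned method can fill.

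**Conclusion.** The point holds as one of efficiency and wording. Item 5 can discard valid week-12 and week-24 recordings when the baseline week does not qualify, and its exclusion phrase leaves patients with 1 to 3 valid baseline days undefined on one reading. If 20% of patients with valid follow-up lack a baseline, the avoidable SE increase is 6-9%; across assumed rates of 5% to 30% it runs from about 1% to 15%. These figures rest on an assumed correlation of 0.5-0.7 and on data missing at random given the imputation model, which item 5 already assumes. The consequence is confined to the exploratory wearable comparison.

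**What to change.** Reword item 5 so that every mITT patient with at least one qualifying wearable week (baseline, week 12 or week 24) enters the multiple imputation analysis, and a baseline with fewer than 4 valid days is treated as missing and imputed in the same model as the follow-up values. This also removes the ambiguous phrase. Keep the present restriction to patients with a complete baseline as a sensitivity analysis. The 4-valid-day threshold can stay as a pre-specified quality rule.

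The cost is a change of wording and a slightly larger imputation model. No new data are needed.

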### Sample size calculation

2.2

This study is a multicenter, randomized, double-blind, placebo-controlled trial. The primary outcome is a continuous variable. The allocation ratio between the SXYX group and the placebo group is 1:1. The sample size will be calculated using the formula for comparing two independent means. The formula is as follows:$$n_{1}=n_{2}=2{\left[\frac{(Z_{\alpha /2}+Z_{\beta })\sigma }{\delta }\right]}^{2}$$Based on preliminary data from a small-sample, exploratory pilot study, the peak oxygen consumption (VO_2_ peak) in patients with HFpEF after 6 months of treatment was 20.2 ± 4.8 mL/kg/min in those receiving Chinese herbal medicine, and 18.9 ± 4.2 mL/kg/min in those receiving standard conventional medical therapy. The standard deviations of 4.8 and 4.2 from the preliminary data were used solely to estimate the population standard deviation (*σ*). Based on the OptimEx-Clin Study (21), the latest prognostic studies of percentage of predicted peak VO_2_ in HFpEF (22), and the published results of traditional Chinese medicine for HFpEF with the Qi-deficiency and blood-stasis pattern (23), the minimal clinically important difference for sample size calculation was set at 2.7 mL/kg/min.$$\sigma^{2}=(S_{{}_{1}}^{2}+S_{2}^{2})/2=(4.8^{2}+4.2^{2})/2=20.34$$$$n_{1}=n_{2}=2{\left[\frac{(Z_{\alpha }+Z_{\beta })\sigma }{\delta }\right]}^{2}=2\left[\frac{{\left(1.96+1.282\right)}^{2}\times 20.34}{2.7^{2}}\right]\approx 59$$The calculation yielded approximately 59 patients per group. Accounting for an anticipated 20% dropout rate, the required sample size was adjusted to 74 patients per group, resulting in a total enrollment of 148 patients.

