
### Missing data and protocol deviation handling

2.17

For the primary endpoint, the MMRM provides valid estimates under the missing-at-random (MAR) assumption using all available observed data. To test the robustness of the MAR assumption, two sensitivity analyses will be performed: (i) complete-case analysis, restricted to patients who completed the full 24-week follow-up; and (ii) worst-case scenario analysis, in which missing values in the SXYX group are imputed with the minimum observed value and those in the placebo group with the maximum observed value. For secondary endpoints with a missing rate >10%, multiple imputation (MI) using a chained-equation approach will be applied, with the imputation model including all covariates and outcome variables. For patients who meet the mITT criteria (i.e., have received at least one dose of the study drug and have at least one post-baseline CPET assessment), if they experience any of the following events—(i) premature discontinuation of the study drug, (ii) receipt of rescue therapy for worsening heart failure (e.g., intravenous diuretics), (iii) hospitalisation for any reason, (iiii) Medication adjustments due to various reasons, or (iiiii) inability to complete CPET—they will still be retained in the mITT set (in accordance with the intention-to-treat principle), but will be excluded from the per-protocol set for sensitivity analyses. All protocol deviations will be summarised and listed by treatment group, and submitted to the Data Monitoring Committee for review in the final report.

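### In the wearable worst-case scenario the printed signs (+2 SD for SXYX, −2 SD for control) contradict the bracketed directions for measures where higher is better

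*Protocol article*

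**What the plan says.** Section 2.15 (Data collection and management), wearable item 5, handles missing wearable data by multiple imputation under missing at random. It then adds a worst-case scenario to explore that assumption. For SXYX, "missing values in the intervention group will be replaced by the group observed mean +2 standard deviations (in the direction of worsening"); for control, "those in the control group by the group observed mean −2 standard deviations (in the direction of improvement").

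Item 6 lists the derived measures: "Mean heart rate, step count (distance), oxygen saturation, heart rate variability, and nocturnal sleep duration". Item 5 does not limit the scenario to some of them, and neither item says which direction is better for any of them.

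The scenario is to be read by "comparing whether the direction and magnitude of the effect estimates are consistent with those of the primary analysis", and "all results will be clearly labelled as exploratory, with no formal statistical significance testing or adjustment for multiplicity".

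For the primary endpoint, section 2.17 has a separate worst-case rule: "missing values in the SXYX group are imputed with the minimum observed value and those in the placebo group with the maximum observed value".

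**The concern.** A mean plus 2 SD is a worse value only where higher is worse. Of the five measures that fits mean heart rate, on the usual reading. For step count, distance and oxygen saturation it is a better value, so the analyst has to choose between the arithmetic and the words in brackets.

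The choice matters because the two codings push the estimate in opposite directions. An analyst who programs the signs fills missing SXYX values with very good results and missing placebo values with very poor ones. The scenario would then seem to confirm or enlarge any SXYX benefit. The rule exists to show whether direction and size hold up under adverse assumptions, and that is the property the sign settles.

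This is also the only check of missing at random stated for the wearable data; the checks in section 2.17 on that assumption concern the primary endpoint. If the direction is settled only after the data are seen, it becomes an avoidable analyst choice.

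**Working it through.** The plan gives no figure for this scenario, so there is none to reproduce. The check compares the two codings.

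**Inputs**
- Imputed values: observed arm mean ± 2 SD (section 2.15, item 5).
- Allocation 1:1 (section 2.2).
- Missing fraction m per arm: the article gives none for the wearable data. Section 2.2 allows for dropout: "Accounting for an anticipated 20% dropout rate, the required sample size was adjusted to 74 patients per group". I use 20% as an illustration only, with a range of 5% to 30%.
- Equal SDs and equal m in the two arms, and unadjusted means (assumptions).
- Direction of benefit: the Abstract and the Discussion present step count and walking distance as measures of exercise tolerance, and the Introduction counts better exercise tolerance as a benefit. Higher is therefore better for step count and distance. For oxygen saturation, higher is better is a clinical assumption, and a safe one.

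**Formula**
Filling a fraction m of an arm at mean + 2 SD gives (1 − m) × mean + m × (mean + 2 SD) = mean + 2m SD. Filling at mean − 2 SD gives mean − 2m SD. For SXYX minus placebo on a higher-is-better measure:
- coded by the signs: shift = +2m SD − (−2m SD) = +4m SD, in favour of SXYX;
- coded by the words: shift = −2m SD − (+2m SD) = −4m SD, against SXYX.

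The codings therefore differ by 8m SD.

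| m per arm (assumed) | By the signs | By the words | Gap |
|---|---|---|---|
| 5% | +0.2 SD | −0.2 SD | 0.4 SD |
| 10% | +0.4 SD | −0.4 SD | 0.8 SD |
| 20% | +0.8 SD | −0.8 SD | 1.6 SD |
| 30% | +1.2 SD | −1.2 SD | 2.4 SD |

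**Check at the planned size.** With 59 observed and 15 missing of 74 per arm, m = 15/74 = 0.203 and 4m = 0.81. An observed difference of +0.30 SD becomes 0.30 + 0.81 = +1.11 SD by the signs and 0.30 − 0.81 = −0.51 SD by the words. A simulation of 4,000 trials gave +1.11 and −0.51. With a true difference of zero it gave +0.80 and −0.81.

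**Limits of the scale.** Oxygen saturation cannot exceed 100%. At mean + 2 SD, an assumed mean of 94 with SD 2 gives 98; 95 with SD 2 gives 99; 96 with SD 2 gives 100; 96 with SD 2.5 gives 101. The impossible value falls in the SXYX arm if the signs are followed and in the placebo arm if the words are followed, so it is a separate boundary problem and no evidence about the sign. Likewise, mean − 2 SD for steps is negative whenever the SD exceeds half the mean.

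**Remaining measures.** For heart rate variability and nocturnal sleep duration the article states no better or worse direction. The bracketed words therefore cannot be turned into a number without a further decision.

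**The case against.** A reader who looks at the signs alone might infer that the plan prespecifies a best case for SXYX and so points its robustness check the wrong way. The article does not support that. It calls the scenario a worst case, the brackets send SXYX towards worsening and control towards improvement, and the parallel peak VO2 rule in section 2.17 gives SXYX the minimum and placebo the maximum. All three are adverse to SXYX. If the plus sign is read as a step towards worsening on each measure's own scale, the sentence is coherent and conservative. The shift in favour of SXYX arises only if the sign is followed and the words are ignored.

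That argument stands as to intent. It does not repair the text: the rule is arithmetic on an observed mean, no recoding to a severity scale is stated, and the reading still needs a direction for sleep duration and heart rate variability.

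It can also be said that coding directions and truncation limits are commonly left to the statistical analysis plan, which is not shown. That is fair for missing detail, but the article has fixed a sign, and for step count and oxygen saturation that sign conflicts with its own label.

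Finally, the stakes are modest. The wearable measures are not among the secondary outcomes in section 2.14.2 or in the fixed testing sequence of section 2.18. The Discussion calls wearable monitoring the study's main innovation, but that gives it no inferential role. This limit on severity stands in full.

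**Conclusion.** The point holds as a contradiction between sign and label. For step count, distance and oxygen saturation the printed arithmetic and the bracketed direction cannot both be obeyed, and the two codings differ by 8m SD: 1.6 SD at an assumed 20% missing per arm, half on each side of the observed difference. The sizes rest on equal SDs, equal missing fractions and unadjusted means. The opposite direction of the two codings does not depend on equality, since in general the shift is 2 × (m × SD in the SXYX arm + m × SD in the placebo arm), with one sign or the other.

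Heart rate variability and sleep duration are undefined rather than shown to be wrong; any claim about their direction would rest on knowledge from outside the article.

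Severity is minor to should-fix. The scenario is descriptive and untested, and neither the primary endpoint nor the four key secondary endpoints are affected.

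**What to change.** In section 2.15, wearable item 5, and in the statistical analysis plan:

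1. Replace the signs: missing SXYX values take the group observed mean moved 2 SD in the unfavourable direction, and missing placebo values take it moved 2 SD in the favourable direction.
2. List the unfavourable direction for each measure: lower for step count, distance and oxygen saturation; higher for mean heart rate, if that is what is meant. For heart rate variability and nocturnal sleep duration, define it or leave the measure out of this scenario.
3. Truncate imputed values at possible limits in both arms: oxygen saturation at most 100%, steps at least 0.

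The cost is a sentence or two and a short list. No new data, visits or patients are needed. It should be done before unblinded wearable data are seen.
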